## Abstract

**Background:**

Patient-reported outcome (PRO) measures have been used widely to screen for depression, anxiety, and symptoms in cancer patients. Computer-based applications that collect patients’ responses and transfer them to the treating health professional in real time have the potential to improve patient well-being and cancer outcomes.

**Objective:**

This study will test the feasibility and acceptability of a newly developed eHealth system which facilitates PRO data capture from cancer patients, data linkage and retrieval to support clinical decisions and patient self-management, and data retrieval to support ongoing evaluation and innovative research.

**Methods:**

The eHealth system is being developed in consultation with 3 overarching content-specific expert advisory groups convened for this project: the clinical advisory group, technical advisory group, and evaluation advisory group. The following work has already been completed during this phase of the study: the Patient-Reported Outcome Measures for Personalized Treatment and Care (PROMPT-Care) eHealth system was developed, patient-reported outcomes were selected (distress, symptoms, unmet needs), algorithms to inform intervention thresholds for clinical and self-management were determined, clinician PRO feedback summary and longitudinal reports were designed, and patient self-management resources were collated. PROsaiq, a custom information technology system, will transfer PRO data in real time into the hospital-based oncology information system to support clinical decision making. The PROMPT-Care system feasibility and acceptability will be assessed through patients completing PROMPT-Care assessments, participating in face-to-face cognitive interviews, and completing evaluation surveys and telephone interviews and oncology staff participating in telephone interviews.

**Results:**

Over the course of 3 months, the system will be pilot-tested with up to 50 patients receiving treatment or follow-up care and 6 oncology staff at 2 hospitals in New South Wales, Australia. Data will be collected to determine the accuracy and completeness of data transfer procedures, extent of missing data from participants’ assessments, acceptability of the eHealth system and usefulness of the self-management resources (via patient evaluation surveys and interviews), and acceptability and perceived usefulness of real-time PRO reporting (via oncology staff interviews) at the completion of the pilot phase.

**Conclusions:**

This research investigates implementation of evidence into real world clinical practice through development of an efficient and user-friendly eHealth system. This study of feasibility and acceptability of the newly developed eHealth system will inform the next stage of larger scale testing and future implementation of the system as part of routine care.

**ClinicalTrial:**

Australian New Zealand Clinical Trials Registry ACTRN1261500135294; https://www.anzctr.org.au/Trial/Registration/TrialReview.aspx?id=369299&isReview=true (Archived by WebCite at http://www.webcitation.org/6lzylG5A0)

## Introduction

Patient reported outcome (PRO) measures have been widely used in a variety of settings including screening for depression, anxiety, and symptoms in cancer patients [1,2] and in the primary care [3] and rural settings [4]. There are many examples of computer-based applications that collect patients’ responses and translate them in real time into a useable format for the treating health professional [1,2,5-8]. A systematic review undertaken by Chen et al [5] concluded that routinely collecting PRO measures enables better patient-centered care in cancer settings when a patient management plan is integrated with routine collection of PROs. This review identified strong evidence that well-implemented electronic PRO (ePRO) systems with timely feedback improved patient–health care provider communication and patient satisfaction and may also improve the monitoring of treatment response and detection of unrecognized problems [5]. The impact of ePROs on clinical and health service outcomes has also now been demonstrated with a large randomized controlled trial with cancer patients reporting significant outcomes including reduced emergency room visits, longer tolerability of chemotherapy, and improved survival [9].

We have previously published a discussion paper citing a lack of ePRO systems being implemented as part of routine oncology care in Australia and detailing our intention to develop an eHealth system, Patient-Reported Outcome Measures for Personalized Treatment and Care (PROMPT-Care), which has the potential to lead to improvements in patients’ quality of life and health outcomes while reducing variations in cancer outcomes [10]. This PROMPT-Care system is based on a prototype system, PROsaiq, which was previously developed to import PRO surveys into a hospital’s Oncology Information System (OIS) [11]. This protocol paper reports on the steps involved in developing this clinical system and the proposed testing of its acceptability and feasibility in 2 oncology care centers. At the time of publication, some of the work described was completed and some was pending.

The purpose of the PROMPT-Care eHealth system is to support the routine collection and analysis of PROs from cancer patients over time, from the time of being registered as a cancer patient, and make this information available to the patient and the health professionals involved in the delivery of their cancer care. The eHealth system will also deliver evidence-based self-management information to address patient-reported problems and empower patients to take a more active role in decision making and managing their ongoing care and recovery. Importantly, one of the key features distinguishing PROMPT-Care from previous eHealth systems used in the oncology setting is its integration into the hospital’s point-of-care OIS.

The term “patient” used throughout this document encompasses all people diagnosed with cancer during and after their acute treatment phase including into longer term survivorship.

## Methods

### Study Design and Objectives

This is a feasibility study with the overall aim of developing and testing an integrated eHealth system to support and enable cancer patients to achieve and maintain improved health and well-being and better cancer outcomes.

The specific objectives are as follows:

1. Develop an eHealth system that is integrated into the hospital’s OIS (MOSAIQ, Elekta Medical Systems, Sunnyvale, CA) to support assessment of cancer patients’ PROs through the use of electronically administered standardized assessment tools, provision of real-time feedback of the results to the treating clinicians, and generation of links to self-management resources for patients that are tailored to their PROs. This includes developing a production version of the PROsaiq prototype system [11].

2. Implement a pilot version of PROMPT-Care at 2 hospitals and test the feasibility and functionality of the system.

3. Test the acceptability of the pilot version of PROMPT-Care in a sample of cancer patients and clinicians at the 2 participating hospitals.

### Setting

The feasibility study will be undertaken in the cancer centers of 2 public hospitals in New South Wales (NSW), Australia. Liverpool Hospital is the largest of the 6 hospitals in South Western Sydney Local Health District, a district with a population of over 820,000 people, comprising 12% of NSW residents. The communities in this district are socially, economically, culturally, and linguistically diverse, and the area contributes 10% of the total new cases of cancer load in NSW. Liverpool Hospital treats more than 81,000 patients annually. Wollongong Hospital is the largest of the Illawarra Shoalhaven Local Health District’s 9 hospitals. This district has a population of more than 390,000 residents. and Wollongong Hospital, the region’s tertiary referral hospital, treats more than 47,000 patients annually.

### Ethics Approval and Consent to Participate

Ethics approval was obtained from the Human Research Ethics Committee of South Western Sydney Local Health District with site-specific ethics approvals obtained for Liverpool Hospital and Wollongong Hospital.

### Development of the PROMPT-Care eHealth System

The PROMPT-Care system includes key features relating to system design, data collection, assessment reporting, and workflow integration that were identified from a review of 33 ePRO systems as being important to supporting a successful ePRO system [1]. We have previously summarized these recommended features [10].

#### Establishing Clinical, Technical and Evaluation Advisory Groups

A total of 3 expert groups were convened to inform the development and evaluation of the PROMPT-Care system: a clinical advisory group (CAG) and a technical advisory group will guide the content, development, and functionality of the system including transformation of PROsaiq from prototype to production, and an evaluation advisory group will guide the feasibility and acceptability testing of the developed system. Additionally, special working groups were convened, as required, to advise on specific aspects of the eHealth system development and content. The membership and roles and responsibilities of these groups are presented in Table 1.

**Table 1 table1:** Patient-Reported Outcome Measures for Personalized Treatment and Care (PROMPT-Care) project advisory group membership, roles, and responsibilities.

Membership and expertise		Roles and responsibilities	Special working groups
**Clinical advisory group**			
	Core members (n=38) with a range of expertise: radiation and medical oncology, nursing, allied health, psycho-oncology, hospital management, cancer systems innovation management, OIS^a^ and electronic records management, and research.	Responsible for the overall content and implementation of PROMPT-Care^b^ as part of routine care, including the clinician feedback system and the patient self-management system. The CAG^c^ is responsible for decisions about: -The outcomes of cancer patients to be collected over time -The PRO^d^ measures to collect the agreed patient outcomes -The frequency of measurement of the PROs -The modes of delivery of the PRO information to health professionals involved in the delivery of patient care in both summary and longitudinal format -The PRO score thresholds which will trigger recommended actions by the clinical team -The content of the evidence-based recommendations to be generated in response to each PRO that is above the predetermined threshold -The suite of evidence-based self-management information that will address patient-reported problems and enable patients to take an active role in decision making and managing their ongoing care and recovery	A clinical algorithms working group will be specifically focused on development of algorithms and evidence-based recommendations for clinicians, which are required for programming the clinician feedback reports. A self-management working group will identify suitable self-management resources for patients using the PROMPT-Care system.
**Technical advisory group**			
	Core members (n=23) with expertise in cancer systems innovation, OIS and electronic records management, hospital information management and technical design, oncology informatics, and medical and radiation oncology.	Responsible for overseeing the development and implementation of the production information technology system (PROsaiq) and infrastructure to support PRO data capture and management including: -Integration of the pilot PROMPT-Care system with the existing hospital information technology systems and OIS to support real-time data access to all members of the care team, including network configuration, with special consideration of hospital security firewalls -Delivery of a patient assessment interface suitable for use on both desktop and mobile technology (eg, tablets) to support PRO data capture either within the clinic or from home at predefined periods	A MOSAIQ reporting working group will be specifically focused on display of the PRO data in MOSAIQ.
**Evaluation advisory group**			
	Core members (n=10), with wide-ranging research and statistical expertise, particularly in psycho-oncology and clinical research.	Responsible for developing an evaluation plan to document the feasibility and acceptability of the PROMPT-Care system.	

^a^OIS: oncology information system.

^b^PROMPT-Care: Patient-Reported Outcome Measures for Personalized Treatment and Care.

^c^CAG: clincial advisory group.

^d^PRO: patient-reported outcome.

#### Selection of Patient-Reported Outcome Measures and Assessment Frequency

The CAG was consulted about which PRO domains were most important for informing patient care and amenable to evidence-based intervention. The CAG was presented with the following domains to consider: symptoms, distress, anxiety, depression, quality of life, and unmet needs. Following the selection of the domains to be assessed, a comprehensive review of specific measures was undertaken to select the final core set of PRO measures. PRO measures that met the following recommended properties were favored for inclusion in the PROMPT-Care survey: simple, brief, informed by patients, reliable, valid and responsive to change, easily scored and interpreted, and free to use as well as those which predicate clinical action [12]. In an effort to minimize patient burden, an item map was developed during this phase to identify any significant duplication of items across the short-listed measures, and any redundant measures were excluded from the core PRO assessment. The final measures selected were: the Distress Thermometer (DT) [13] with the problem checklist [14], the Edmonton Symptom Assessment Scale (ESAS) [15] and the Supportive Care Needs Survey–Screening Tool 9 (SCNS-ST9) [16]. However, it is noteworthy that once the system has been set up and tested, changes in the PRO measures can be made in the future (ie, the initial decisions regarding PROs are not locked in long-term).

The CAG was also consulted about the frequency of patients completing the PRO assessments, with consideration given to (1) the timeframe for the response options for each of the selected PRO measures (eg, within the past week), (2) allowing sufficient time between 2 assessments for clinical recommendations to have been actioned, (3) minimizing patient burden and therefore improving compliance, and (4) whether the assessment frequency should differ for patients on-treatment versus those in follow-up. The CAG advised on the frequency of assessments for this phase of the PROMPT-Care program while acknowledging that the feasibility and acceptability testing would inform future assessment frequency.

#### Development of Algorithms to Guide Response to Patient-Reported Outcomes

For each of the selected PRO measures, item and scale cut-off scores differentiating between normal (below threshold) and clinical (above threshold) responses were determined from published sources [14,16,17]. These threshold scores informed the development of clinical and self-management recommendations. A multidisciplinary clinical algorithms working group was convened (medical and radiation oncologists, social worker, clinical psychologist, care coordinators) to develop actionable recommendations for each item that breaches the clinical threshold. A total of 15 actionable recommendations were developed after consultation with published guidelines [14,18]. These recommendations were tailored to the specific issue of concern (eg, symptom vs information need), and they ranged from “No action required” to “Clinically address as appropriate OR refer to [*types of specialties indicated here, depending on issue*] for further assessment and care.”

#### Development of Patient-Reported Outcome Feedback Reports

The PROMPT-Care system is designed to allow any oncology staff member from the participating cancer centers to access their patients’ PRO assessment reports. A total of 2 report formats were developed in consultation with the CAG members: (1) a summary report of the patient’s most recent PROMPT-Care survey, which included recommendations for the care team to address the patient-reported concerns and (2) a longitudinal report summarizing the PROs over time to allow the clinical team to identify trends and determine whether previously implemented interventions have addressed patients’ issues of concern. Consideration was given to the content and presentation of the feedback reports with a focus on minimizing any need for interpretation of scores and highlighting issues of concern (scores above predetermined thresholds) in red to readily draw attention to them. Refer to Multimedia Appendices 1 and 2 for examples of the clinician summary and longitudinal feedback reports.

#### Collation and Review of Patient Self-Management Resources

The PROMPT-Care assessment measures items in the domains of physical well-being (eg, fatigue, pain, mouth sores), emotional well-being (eg, anxiety, depression, loss of interest in activities), social and family well-being (eg, support from family and friends, problems with partner), and practical support (eg, transport, housing, being informed about test results). A self-management working group was established as a subgroup of the CAG to identify suitable, readily available self-management resources in each of these domains as well as in the “maintaining health and well-being” domain for general health issues. Identified resources were systematically reviewed on the basis of their quality (language used, links active and relevant, peer-reviewed resource, HonCode certification [19], currency, applicability and objectivity). Each resource was reviewed by a member of the working group, and the results were collated on an evaluation form that outlined whether or not the resource was to be included in the pilot project. Resources were sought from local NSW cancer websites and organizations in the first instance followed by reputable Australian sources and finally from international cancer organizations. These self-management resources will be accessible to participating patients via 5 domain-specific pages hosted on the Cancer Institute NSW (CINSW) eviQ website [20], with patients’ responses to the PROMPT-Care assessment determining which pages they were able to access.

### Participants

As this is a feasibility study, staff will be selected on the basis of their willingness to comprehensively test the PROMPT-Care system and provide feedback to inform any modifications required for the next phase of research. Clinicians will be asked to identify eligible patients for the pilot study who they perceive would also be willing to provide comprehensive feedback on the pilot PROMPT-Care system. Hence, the participant selection was purposive rather than representative.

Eligible patients are people who are either currently receiving cancer care (including follow-up care) or have recently been diagnosed with cancer and are scheduled to commence cancer treatment at one of the participating sites. Eligibility criteria include a confirmed diagnosis of cancer, age 18 years or over, cognitively able to provide informed consent and understand the surveys, and sufficient skills to complete the survey in English. Exclusion criteria are having a diagnosis of a blood cancer and not having access to the Internet outside of the clinic.

All staff who provide care in the oncology departments at the participating hospitals are eligible to participate. However, as this is a small feasibility study, 3 clinicians from each hospital (6 in total) who were not directly involved in the development of any aspects of the PROMPT-Care system will be invited to participate. In this phase of research, only 3 staff were ineligible to participate due to their direct, rather than advisory, role in building the technical or clinical components of the PROMPT-Care system.

### Measures

The system’s functionality will be assessed over a 3-month period with some patients expected to complete only 1 PROMPT-Care assessment during this period (if recruited later in the study) and some completing up to 3 assessments (if recruited at the start of the study).

The accuracy and completeness of data transfer procedures (from the point of the patient completing an assessment to a report appearing via MOSAIQ) will be assessed by comparison of data received by MOSAIQ to data presented in the clinical feedback reports.The extent of missing data from participants’ assessments will be assessed through examination of the PROMPT-Care reports to determine whether there is any systematically missing data.

In this study, the main purpose of assessing acceptability is to identify any modifications necessary for improving patient and provider uptake of the system in the next phase of research. Hence, acceptability of the system to patients and staff will be assessed as follows:

Patients will complete an evaluation survey and interview at the end of the pilot phase to determine their perceptions of acceptability of the eHealth system and usefulness of the self-management resources.Cancer center staff directly involved in the pilot phase will participate in an evaluation interview at pilot study completion. The interview will focus on their perceptions of the acceptability and perceived usefulness of the real-time PRO reporting.

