## Results

Descriptive data will be collected to inform accuracy and completeness of data transfer from the PROMPT-Care surveys to the OIS. All interviews with patients and oncology staff will be audiorecorded and transcribed verbatim with quotes extracted indicating patient and staff reflections on their engagement with the PROMPT-Care system and identification of access barriers or problems. Cognitive interviews will be reviewed and patient cognitive errors identified to highlight potentially problematic elements of the survey.

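### The data-transfer check compares MOSAIQ only with the feedback reports, so it cannot detect loss or error between survey submission and MOSAIQ

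*Protocol article*

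**What the plan says.** The Measures section of the protocol article defines the path to be verified as running "from the point of the patient completing an assessment to a report appearing via MOSAIQ". The same sentence gives the method: accuracy and completeness "will be assessed by comparison of data received by MOSAIQ to data presented in the clinical feedback reports". The extent of missing data, in the next sentence, "will be assessed through examination of the PROMPT-Care reports to determine whether there is any systematically missing data".

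The Results section describes the target as the transfer between surveys and the oncology information system (OIS): "Descriptive data will be collected to inform accuracy and completeness of data transfer from the PROMPT-Care surveys to the OIS". It names no reference record. The abstract states the aim, also without a comparator: "Data will be collected to determine the accuracy and completeness of data transfer procedures".

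Two other places fix the terms. The first objective, under Study Design and Objectives, identifies the OIS as MOSAIQ. The abstract's Methods paragraph says what carries the data there: "PROsaiq, a custom information technology system, will transfer PRO data in real time into the hospital-based oncology information system".

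**The concern.** The scope in the Measures sentence is wider than its method. The scope begins with the patient's completed survey, whereas the comparison begins with what MOSAIQ has already received. The leg left out is the one PROsaiq performs. PROsaiq is being taken from prototype to production for this project, and Table 1 asks for special attention to hospital firewalls when the system is integrated.

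Followed as written, the pilot could report complete agreement while items or whole assessments were being lost or altered on their way into the OIS. The pilot's conclusions are meant to inform larger-scale testing, and clinicians are instructed to review and discuss the flagged scores during the consultation. A transfer result that says nothing about the survey-to-MOSAIQ leg would be a weak basis for either.

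**Working it through.** The plan states no figure to reproduce, and the point is one of logic. Label the stages as follows:

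- A: the answers as the patient submitted them
- B: the data received by MOSAIQ
- C: the data shown in the feedback report

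The passages, side by side:

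- Scope of the check (Measures): A to C.
- Comparison specified (Measures): B against C.
- Source for missing data (Measures): C.
- Transfer named in Results: surveys to OIS. The OIS is MOSAIQ, so this is A to B.
- Any comparison that uses A as the reference: none in the article.

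Taking each kind of fault in turn:

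| Fault | At B | At C | B against C | A against B |
|---|---|---|---|---|
| Item altered or mis-mapped between A and B | wrong value | same wrong value | agrees | differs |
| Item lost between A and B | blank | blank | agrees | differs |
| Whole assessment never reaches MOSAIQ | absent | absent | not in the comparison | unmatched submission |
| Assessment filed to the wrong patient | wrong record | report for the wrong record | agrees | differs on patient |
| Fault between MOSAIQ and the report | correct | wrong | differs | agrees |

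Only the last row is visible to the stated comparison. For the first four, the chance that B against C shows a discrepancy is 0, whatever the fault rate.

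The missing-data check has the same limitation. A blank at C can arise because the patient skipped the item (blank at A) or because it was lost in transfer (present at A, blank at B). Without A the two cannot be told apart.

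Scale: the abstract gives up to 50 patients, and Measures expects between 1 and 3 assessments each. At full recruitment that is 50 × 1 = 50 to 50 × 3 = 150 assessments. The article does not state a total, and the conclusion is the same at either end.

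**The case against.** The strongest reply is that this is a condensed article. Table 1 gives the evaluation advisory group the job of writing an evaluation plan, which is not shown, and the Results section shows that the authors do intend to report on survey-to-OIS transfer. What stands is that the aim is present. A reader might infer that the leg was simply forgotten, and the Results sentence does not support that. The article does not, however, leave the method to another document. It states one, and that method does not measure the stated target. If the sentence is only loosely worded, it still needs correcting.

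A second reply is that faults could surface in other ways. Each participant has an assessment schedule, and home surveys not completed within 48 hours prompt a reminder. The first assessment is done at the clinic with research staff on hand. Clinicians open the report with the patient present. Staff are interviewed about technical issues, and a subset of first completions is recorded for the cognitive interviews. This stands in part. A reader might infer that the study as a whole is blind to upstream faults, and that goes too far: an absent report or an implausible flag could be noticed. None of these routes is the stated measure, and none reconciles items systematically.

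A third reply is that this is a small, purposive, descriptive pilot. That is correct ("This is a feasibility study with the overall aim of developing and testing an integrated eHealth system") and it bears on how elaborate the remedy should be. It does not make the present comparison informative about the omitted leg.

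**Conclusion.** The point holds. The stated check covers MOSAIQ to report only, although its declared scope starts with the patient's completed survey. Its sensitivity to faults between submission and MOSAIQ is nil by construction, and the missing-data check cannot separate skipped items from lost ones.

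This rests on one reading: that the report is drawn from data held in MOSAIQ. The order of the path in Measures, and the working group in Table 1 for displaying these data in MOSAIQ, support it. Even if the reports were built elsewhere, the patient's submitted answers would still not be the reference.

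Two stronger conclusions are not supported. A reader might take transfer accuracy to be the main feasibility endpoint. The article lists it beside missing data and acceptability, ranks none of them and ties no progression threshold to it, so a wrong decision to scale up cannot be said to follow. A reader might also want a probability that a source comparison would catch a fault. That needs an assumed fault rate, an assumed number of assessments and independent faults. A mis-mapped item would recur in every assessment that contains it, so independence is not credible for that kind of error.

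**What to change.** Replace the comparison in Measures with a two-step reconciliation of every submitted assessment:

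1. Compare the survey-side record (the submission and its item responses) with MOSAIQ by patient, time and item.
2. Compare MOSAIQ with the feedback report by item, including the threshold flags.

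Report descriptively for each leg: assessments received out of those submitted, and items matching source out of items compared. Summarise errors both by item and by assessment, so that a systematic mapping error is distinguishable from scattered losses. Take missing-data counts from the survey-side record, so that patient skips are separated from transfer loss. Confidence intervals are not needed for a descriptive aim. If any are given, they should allow for items clustered within assessments and patients.

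The cost is a short change of wording and a reconciliation of about 50 to 150 assessments at full recruitment. It also depends on a survey-side record, and the article does not say that one is kept. Reminders for incomplete home surveys and emailed links chosen from the responses imply that completion and answers are processed somewhere, but not that they are stored. If they are not, retention for the pilot must be arranged before it starts, because the source data could not be assumed recoverable afterwards. Comparing stored records should ask nothing further of patients.
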